#### Additional analyses

2.5.3

For a more detailed evaluation, additional statistical tests will include the analyses of potential moderators or confounding variables. Thus, we will check for possible pre-treatment differences between IG and CG in healthcare service utilization, demographic variables, and eating disorder symptom severity by conducting independent *t*-tests and chi-square tests. In case of significant group differences, these variables will be added as moderators of the treatment × time interaction effects to test the robustness of the findings. Further covariates possibly affecting the primary outcomes such as patient outcome expectancies, patient adherence, satisfaction, attitudes towards psychological online interventions, or emotion regulation will be included in our analyses.

Moreover, we will analyze the weekly assessments of eating disorder symptoms and the data from the EMA. This will allow us to examine changes in core eating disorder symptoms with a higher ecological validity and temporal resolution. As patient safety indicators, the percentage of participants in the IG who experienced adverse intervention effects caused by the intervention will be quantified, and the amount of impairment due to these adverse effects will be calculated. Further, changes in emotion regulation difficulties and strategy use in patients both on a habitual level and in daily life will be evaluated as potential moderators and mediators of symptom reduction in BN.

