#### Randomization and blinding

2.3.1

Each participant completing the baseline assessment will be randomized by an independent researcher not involved in the project using a computer-based algorithm provided by the online platform *SoSci Survey* (Leiner, 2021) with a 1:1 ratio. Participants will be automatically informed about the randomization result. Therefore, interviews will be conducted blindly, as the clinical interviewers do not know to which group the interviewed participant will be allocated (allocation sequence concealment; Altman and Schulz, 2001). Participants are not explicitly informed that there is an intervention and a control group; instead, they are told that the waiting period for the intervention randomly varies between 0 and 12 weeks. After randomization, each participant will immediately receive an email either including the access code for the intervention (IG) or the information that the intervention will start in 12 weeks (CG).

Group allocation will be masked during the data analyses to minimize possible bias concerning the statistical procedure. For this purpose, an independent researcher will delete all information in the data set indicating the group allocation. Therefore, the evaluator does not know which expression of the group variable represents the IG or the CG.

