#### Primary and secondary outcome analyses

2.5.1

For the statistical analyses of the effectiveness of the web-based intervention for patients with BN, growth models within a mixed linear models (MLM) framework will be performed. These have the advantage of considering the multi-level data structure of three repeated assessments (level 1) as nested within patients (level 2) and treating the outcome change as a continuous process. Additionally, MLMs have more power when handling missing data than traditional approaches (Hesser, 2015; Kahn and Schneider, 2013; Tasca and Gallop, 2009). To evaluate whether there is a significant treatment × time interaction effect, we will follow a stepwise procedure by running models of increasing complexity (Kahn and Schneider, 2013). First, a random intercept model without predictors will be conducted, then we will add fixed effects of time (study entrance, 6 weeks, 12 weeks) and treatment (IG vs. CG) into the second model. Finally, the treatment × time interaction will be included to evaluate whether the outcome change differs between the IG and the CG. Likelihood ratio tests and the Akaike Information Criterion will be used to compare the fit of these three models. A significant treatment × time-interaction with more substantial changes in the intervention group compared to the waitlist group will confirm the hypotheses (Raudenbush and Bryk, 2002). The magnitude of treatment effects will be estimated following the suggestions for Cohen's *d* by Feingold, 2009, Feingold, 2013.

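### Section 2.5.3 picks the variables for its robustness check by baseline significance tests and enters them as moderators, so the check is triggered by chance and answers a different question

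*Protocol article*

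**What the plan says.** Section 2.5.3 (Additional analyses) sets out a two-step rule. The arms are first compared at baseline for "pre-treatment differences between IG and CG in healthcare service utilization, demographic variables, and eating disorder symptom severity", "by conducting independent *t*-tests and chi-square tests". Then: "In case of significant group differences, these variables will be added as moderators of the treatment" × time effect, with the stated aim "to test the robustness of the findings".

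The confirmatory analysis is in section 2.5.1. It is a growth model with time and treatment, to which "the treatment × time interaction will be included to evaluate whether the outcome change differs between the IG and the CG". It names no baseline covariates. Section 2.3.1 says allocation is by computer algorithm "with a 1:1 ratio".

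Section 2.5.3 does not give the number of variables screened, the significance level of the screen, or whether moderators are centred. Section 2.5.2 separately names four baseline variables as imputation predictors, among them BMI, the binge count from the EDE interview and years since illness onset.

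**The concern.** The rule has three faults, and none of them depends on how the model is coded.

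- **The trigger is chance.** In a properly randomised trial the null hypothesis behind a baseline comparison is true by design. A significant result therefore shows that a chance imbalance occurred, and the content of the robustness check depends on that accident.
- **The selection ignores prognosis.** An imbalance matters for the effect estimate only to the extent that the variable predicts the outcome. A between-arm p-value does not measure this. An irrelevant variable at p = .04 enters and a strongly prognostic one at p = .06 does not.
- **The model does not match its purpose.** A moderator of treatment × time is a three-way interaction. It asks whether the effect differs across levels of the variable. Robustness to imbalance asks whether the overall effect survives adjustment, which needs the covariate and its interaction with time but no crossing with treatment.

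A fourth problem is conditional. Once the three-way term is in the model, the treatment × time coefficient is the effect at moderator value zero. Without centring, that value may lie far from the data, and the coefficient cannot be set beside the primary one.

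At stake is the reading of the supporting analysis. A sound primary result could seem to fail its robustness check, or a subgroup contrast could be reported as evidence of robustness.

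**Working it through.** **Inputs from the article.** d = 0.50, intraclass correlation .40, power .80, alpha .05, N = 152 (section 2.6); three assessments at 0, 6 and 12 weeks (section 2.5.1); 1:1 allocation (section 2.3.1). **Assumed:** two-sided tests, a screening level of .05, independent screened variables, and 3 to 20 of them.

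**1. Reproducing the plan's sample size.** Take a random-intercept linear growth model with times 0, 0.5 and 1 and total variance 1.
- Residual variance = 1 − 0.40 = 0.60; sum of squares of time = 0.5.
- SD of a person's slope = √(0.60/0.5) = 1.095.
- n per arm = 2 × (1.960 + 0.842)² × 1.2 / 0.50² ≈ 75.4, so 76 per arm and N = 152, with power 0.803. This matches the article.
- SE of treatment × time = 1.095 × √(2/76) = 0.178.

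**2. How often the rule fires.** The probability that at least one of k variables is significant is 1 − 0.95^k.

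| Variables screened | Probability |
|---|---|
| 3 | 14% |
| 5 | 23% |
| 10 | 40% |
| 15 | 54% |
| 20 | 64% |

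**3. What centring does.** With a full treatment interaction, the SE of the treatment coefficient at moderator zero is approximately 0.178 × √(1 + m²), where m is the distance from zero to the moderator's mean in SD units. For m = 2 this is 0.178 × √5 ≈ 0.40. For m = 0 (mean-centred) it stays at 0.178.

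**4. Simulation.** There were 6,000 trials per scenario, with 76 per arm, true effect 0.50, 5 or 10 independent continuous baseline variables, and either no moderation or moderation of 0.2 per SD by one variable. Results among trials in which the screen fired:

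| Model | Mean estimate | SE | Power |
|---|---|---|---|
| Unadjusted | 0.49–0.51 | 0.18 | 0.79 |
| Selected variables as covariates of change | 0.49–0.50 | 0.18 | 0.76–0.79 |
| Moderators, mean-centred | 0.49–0.51 | 0.18 | 0.76–0.79 |
| Moderators, uncentred, zero 2 SD below mean | 0.44–0.51 | 0.42–0.45 | 0.20–0.22 |

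The estimates near 0.44 arise in the scenarios with true moderation. The simulated SE exceeds the 0.40 of step 3 because these trials are imbalanced by selection and some have more than one variable selected. No variable was given a prognostic effect common to both arms, so the table does not show any precision that prognostic covariates could add.

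**The case against.** The strongest reply is that little harm follows. The rule sits under additional analyses and replaces nothing; section 2.5.1 fixes the confirmatory test without it. Centring is a coding detail that an article can leave to its analysis script, which section 2.5 places in a supplement that is not shown. With centring, the average effect is recovered. For categorical variables and service-use counts, zero can be a real, observed value. Section 2.5.3 also speaks of moderators as well as confounders, and its next sentence brings in further covariates thought to affect the primary outcomes, regardless of any baseline test.

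Much of this stands. It confines the point to a supporting analysis and makes the loss of precision conditional. It does not rescue the rule: with perfect centring, variables are still chosen by a chance event, and the model still asks about effect modification when the stated aim is robustness. The further covariates in the next sentence include post-randomisation quantities such as adherence and satisfaction, so that list is not a baseline adjustment set.

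A reader might infer something stronger: that the rule necessarily ruins the treatment coefficient. For instance, with uncentred BMI (assumed mean 23, SD 4) the SE becomes 0.178 × √(1 + (23/4)²) ≈ 1.04 and power falls to about 7–8%. The article does not support this as a consequence of the plan. Section 2.5.3 does not name BMI among the screened variables, the mean and SD are assumptions, and nothing says that moderators will be left uncentred.

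**Conclusion.** The point holds for the robustness analysis in section 2.5.3 only. Selection by baseline significance test, and entry as a moderator instead of a covariate, are wrong for the stated purpose whatever the coding. The chance of triggering runs from about 14% to 64% for 3 to 20 variables, assuming independent tests at .05; correlated symptom measures would change these figures.

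The loss of precision is a conditional risk. It is large if moderators are uncentred and zero lies 2 SD from the mean (power 0.20–0.22), worse if zero is further away, and essentially absent if they are mean-centred.

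A reader might also infer that the trial's main conclusion or sample size is compromised. It is not: the primary test, its type I error and N = 152 do not depend on this rule. The change is worth making because a better method is available at almost no cost.

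**What to change.** Reword section 2.5.3 as follows.

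- Report baseline characteristics by arm descriptively. Delete the t-tests, the chi-square tests and the trigger that depends on them.
- Make the robustness check a single adjusted model with a short covariate set fixed in advance from data already collected. Candidates are variables that section 2.5.2 already uses for imputation: BMI, the EDE-interview binge count and years since onset. The authors should confirm that these are expected to be prognostic, since the article lists them only as imputation predictors.
- Enter each covariate as a main effect and by time, not crossed with treatment, so that the treatment × time coefficient stays comparable with the primary one.
- Keep moderator analyses as a separate set, named in advance, with mean-centred moderators, and labelled exploratory.

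The cost is a rewording of one section and a matching edit to the analysis script. No new data are needed and the sample size does not change. If the outcome data have already been seen by arm, the covariate set should be reported as chosen afterwards.

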
#### Other measures

2.4.7

•Attitudes towards psychological online interventions: Two subscales of the *Attitudes Towards Psychological Online Interventions Scale* (APOI; Schröder et al., 2015) will be used. The selected subscales consist of eight items rated on a 5-point scale and are validated as reliable measures of perceived technologization threat (Cronbach's α = .64) and anonymity benefits (Cronbach's α = .62) of online interventions (Schröder et al., 2015).•Patient outcome expectancies: Treatment motivation will be assessed using the *Patients' Therapy Expectation and Evaluation Scale* (PATHEV; Schulte, 2008). The PATHEV consists of 16 items answered on a 5-point scale and has been revealed to reliably measure treatment motivation (α > .73; Schulte, 2005).•Negative intervention effects: The *Negative Effects Questionnaire* (NEQ; Rozental et al., 2019) will be used to capture the occurrence of adverse intervention effects. For each of the 32 items of the NEQ, participants answer whether an adverse effect occurred (yes/no), how strong the effect was (0 to 4) and whether they attribute the negative effect on the treatment or something else. Two scores can be obtained, one for the frequency of adverse effects due to treatment, ranging from 0 to 32, and one for the negative impact, ranging from 0 to 128. The NEQ has been established as a valid and reliable measure and has an internal consistency of Cronbach's α = .95 (Rozental et al., 2019).•Use of other healthcare services: To measure access to healthcare as well as the use of other healthcare services, the *Client Sociodemographic Service Receipt Inventory – European Version* (CSSRI-EU; original: Chisholm et al., 2000; Roick et al., 2001) will be used, which is a valid and reliable measure to assess the number and length of different types of healthcare service contacts (e.g., number of therapy sessions and contact with psychotherapists and psychiatrists).•Patient adherence: The log files on the *Selfapy* platform will be employed to capture patient adherence. This includes the number of times and dates a participant logs into the web-based intervention and the number of completed modules. Additionally, participants in the IG will be asked how many times they used the intervention in the study assessments after six and 12 weeks.

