### Statistical power and sample size

2.6

Sample size estimations were based on meta-analytic evidence for the effectiveness of psychological interventions for BN (Beintner et al., 2014; Haderlein, 2022; Svaldi et al., 2019). Due to the high heterogeneity of effect sizes ranging from medium to large (Beintner et al., 2014; Haderlein, 2022; Svaldi et al., 2019), the sample size needed to detect at least an effect of medium magnitude was estimated using the R package *powerlmm* (Magnusson, 2018). A power analysis with an effect size of *d* = 0.50, an intraclass-correlation of .40 (Arend and Schäfer, 2019), a power of .80, and an alpha-level of .05 resulted in a required sample of *N* = 152. Further power analyses, including possible dropouts, different effect sizes, and intra-class correlations, can be found in the supplementary materials (Figure S2), strengthening our conclusion that our sample size will be sufficiently large to detect a medium effect under different assumptions.

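### Section 2.5.3 admits adherence and satisfaction as covariates, and changes in emotion regulation as moderators, although these arise after randomisation; this can distort the supplementary analyses, not the confirmatory test

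*Protocol article*

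**What the plan says.** Section 2.5.1 sets the confirmatory analysis: a mixed linear growth model with time, treatment and their interaction, judged on the interaction. No other covariate is named.

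Section 2.5.3 (Additional analyses) first plans tests for pre-treatment differences between the arms; variables that differ significantly enter as moderators of the treatment × time effect, as a robustness check. The next sentence adds that further covariates which might affect the primary outcomes, "such as patient outcome expectancies, patient adherence, satisfaction, attitudes towards psychological online interventions, or emotion regulation will be included in our analyses". It gives no time point, model or restriction to one arm. Later in the section, changes in emotion regulation difficulties and strategy use "will be evaluated as potential moderators and mediators of symptom reduction in BN".

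Section 2.4.7 defines adherence by platform log files (log-ins and completed modules). In addition, "participants in the IG will be asked how many times they used the intervention" at six and 12 weeks. Under section 2.3.3 the control group (CG) has no access to the program for those 12 weeks. No satisfaction instrument appears in section 2.4 or Table 2. Table 2 does schedule the expectancy scale (PATHEV), the attitude scale (APOI) and both emotion-regulation scales (DERS, HFERST) at study entrance.

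**The concern.** Adjusting a randomised comparison for baseline variables is harmless and often useful. Adjusting it for something that follows from treatment changes the question: the treatment × time coefficient no longer measures the effect of offering the program.

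- **Adherence** has no baseline reading. Every control is zero or undefined, so arm and adherence compete for the same information.
- **Satisfaction** with the program can exist only after exposure to it, and the article does not say how it would be measured.
- **Changes in emotion regulation** are an intended result of the program: section 2.1 lists emotion regulation among its targets, and section 1.1 among the possible mechanisms of change. The same change score cannot serve both as a mediator of the treatment effect and as a moderator of the randomised comparison.

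At stake is how the robustness and moderator results are read. A real effect could seem to vanish once adherence is added and be called fragile, or a biased adjusted estimate could be taken as corroboration. Section 1.1 makes the influence of patient characteristics and the mechanisms of change the trial's second goal, so this touches a declared objective.

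**Working it through.** **The plan's own figure.** Section 2.6 gives the inputs: "A power analysis with an effect size of *d* = 0.50", "an intraclass-correlation of .40", "a power of .80, and an alpha-level of .05 resulted in a required sample of" *N* = 152. Allocation is "with a 1:1 ratio" (section 2.3.1) and there are three assessments (section 2.5.1). Sidedness is not stated; two-sided is assumed.

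- Code time as 0, 1, 2, so the sum of squares about the mean is 2. Set total variance to 1.
- SD of a participant's slope: √((1 − 0.40)/2) = 0.548. Slope difference: 0.50/2 = 0.25.
- n per arm = 2 × (1.960 + 0.842)² × 0.548²/0.25² ≈ 75.4, rounded up to 76, so N = 152. The stated size is reproduced.
- With three equally spaced times this matches a baseline-to-week-12 change score with variance 2 × 0.60 = 1.2 (SD 1.095). The standard error of the unadjusted arm difference is 1.095 × √(2/76) = 0.178.

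This is the setting for the illustrations below: 76 per arm, true effect -0.50, 4,000 simulated trials unless stated. Adherence distributions, mediated shares and the common cause are assumptions; the article gives none of them.

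**Adherence.** Assume modules completed in the IG have mean 7 and SD 3, cut to 0–12, with 0 in the CG, and that the whole effect is proportional to modules.

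- Adding modules to the model gives an arm coefficient of about 0.00, with rejection in 4.6% of trials. The correlation of adherence with arm is 0.87.
- With mean 6 and SD 3.5 (2,000 trials), the unadjusted estimate is -0.49 (SE 0.18, rejection 79%). Adjusted, it is +0.01 (SE 0.29, rejection 4.8%). The correlation is 0.80.
- The zero follows from the assumption of full proportionality. If only a share q runs through modules, the adjusted coefficient is (1 − q) × (-0.50).
- The loss of precision does not depend on q. At a correlation of 0.87 the standard error grows by 1/√(1 − 0.87²) ≈ 2.03, to 0.178 × 2.03 ≈ 0.36. Even at q = 0, power would be about Φ(0.50/0.36 − 1.96) = Φ(-0.57) ≈ 28%.

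**A post-randomisation mediator.** Assume treatment shifts emotion regulation by 0.5 SD and a share of the effect passes through it. Adjusting for the post-randomisation value gives:

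| Share through the variable | Adjusted estimate | Rejection rate |
|---|---|---|
| 0% | -0.50 | 77% |
| 25% | -0.37 | 54% |
| 50% | -0.25 | 34% |
| 75% | -0.13 | 16% |
| 100% | 0.00 | 4% |

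Unadjusted, the estimate stays at -0.50 and the rejection rate at 79% to 81% throughout.

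**Common cause, no true effect.** Let an unmeasured factor load 0.5 on the variable and -0.5 on the outcome. Within arm, the slope of outcome on the variable is 0.5 × (-0.5) = -0.25, so the adjusted arm coefficient is 0 − (-0.25 × 0.5) = +0.125. The simulation gave +0.12, with a rejection rate of 10.5% against 4.9% unadjusted. Bias can therefore also run away from zero.

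**The case against.** The best defence is that the confirmatory result is safe, and that stands. Section 2.5.1 fixes a model without these covariates and ties the hypotheses to it, section 2.5 places moderator and mediator work in a separate fourth step, and the disputed sentences come under additional analyses. A reader might infer that the plan removes the randomised effect, or that an adjusted estimate will be presented as the primary result. Nothing in the article says so.

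A reader might also take emotion regulation as a covariate to mean its post-randomisation value. The sentence gives no time point, follows sentences about pre-treatment differences, and baseline values exist for emotion regulation, expectancies and attitudes. That is ambiguity, not error. Nor does the article call changes in adherence or satisfaction moderators; it says this only of changes in emotion regulation. Studying those changes as mediators is a legitimate exploratory aim.

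Two further defences carry less weight. Since adherence is recorded only in the IG, an IG-only analysis may be intended, and the supplementary R script, not shown here, may specify one. But the text lists adherence among covariates for the primary outcomes, directly after terms to be added to the two-arm model, and states no such limit. It is also fair that the simulated sizes follow from their assumptions. They show what could happen, and the text as written does not prevent it.

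**Conclusion.** The point holds for three items: adherence and satisfaction as covariates without restriction to the IG, and changes in emotion regulation as moderators. For expectancies, attitudes and emotion regulation as covariates, the fault is only an unstated time point.

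The harm is confined to the supplementary robustness and moderator analyses. There, a true effect of -0.50 could be estimated anywhere between -0.50 and 0.00, depending on the share running through the variable; a common cause could bias it in either direction. These sizes rest on assumed adherence distributions, mediated shares and loadings. That adherence is absent in the CG, and that treatment is meant to change emotion regulation, rest on the article itself. The confirmatory test and N = 152 do not change. The correction is worth making before the data are analysed.

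**What to change.** Reword the two sentences in section 2.5.3:

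- In two-arm models, limit covariates and moderators of treatment × time to study-entrance values (PATHEV, APOI, DERS, HFERST).
- Analyse adherence within the IG only, as a descriptive dose-response relation, or estimate a complier-average causal effect with arm as the instrument, stating the assumption that the offer acts only through use of the program.
- Name a satisfaction measure and use it within the IG, or drop the item.
- Use changes in emotion regulation only as mediators, in a separate mediation analysis (for example, week-6 mediator and week-12 outcome), and remove the word moderators for change scores.
- State that the section 2.5.1 model without these covariates remains the primary analysis.

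The cost is two reworded sentences and a matching change to the R script. Unless a satisfaction measure is added, no new data are needed, and the sample size stays the same.

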#### Outcomes

2.4.3

Primary and secondary outcome measures will be assessed at baseline (study entrance), six weeks after baseline (mid-treatment), and 12 weeks after baseline (post-treatment). Moreover, eating behavior, binge eating episodes, and compensatory behavior will be monitored weekly to assess changes in symptoms with a higher resolution. EMA will be scheduled pre- and post-treatment to measure eating disorder symptoms in daily life. All measures will be collected online using the assessment platform *SoSci Survey* (Leiner, 2021) and made available to participants at http://www.s2survey.net/. An overview of the clinical outcome measures over time based on the SPIRIT guidelines (Chan et al., 2013) is provided in Table 2.

**Table 2 t0010:** SPIRIT schedule of the randomized controlled trial

	Study period				
	Enrollment	Allocation	Post-allocation		Close-out
		*Study entrance*	*Weekly*	*Mid-treatment*	*Post-treatment*
Timepoint	*−t*_*1*_	*t*_*1*_	*t*_*1*_–*t*_*12*_	*t*_*2*_	*t*_*3*_

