**Other measures**					
Client Sociodemographic Service Receipt Inventory (CSSRI)		*+*		*+*	*+*
Negative Effects Questionnaire (NEQ)				*+*	*+*
Attitudes Towards Online Interventions (APOI)		*+*			*+*
Patients' Therapy Expectation and Evaluation Scale (PATHEV)		*+*		*+*	*+*

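### Both safety indicators are intervention-arm only and rest on the participant's own attribution; no between-arm comparison of individual deterioration is stated

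*Protocol article*

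**What the plan says.** Section 2.5.3 (Additional analyses) of the protocol article names two patient safety indicators. One is that "the percentage of participants in the IG who experienced adverse intervention effects caused by the intervention will be quantified"; the other is that "the amount of impairment due to these adverse effects will be calculated".

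Section 2.4.7 (Other measures) explains where the cause comes from. For each of the 32 NEQ items the participant says whether an effect occurred, how strong it was, and "whether they attribute the negative effect on the treatment or something else". Two scores follow: "one for the frequency of adverse effects due to treatment, ranging from 0 to 32", and a negative-impact score from 0 to 128.

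Table 2 schedules the NEQ at mid- and post-treatment. The table has no arm columns, and the article does not say whether waitlist participants complete the questionnaire.

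On efficacy, section 2.4.3 states: "Primary and secondary outcome measures will be assessed at baseline (study entrance), six weeks after baseline (mid-treatment), and 12 weeks after baseline (post-treatment"). Section 2.5.1 then fits mixed models in which "the treatment × time interaction will be included to evaluate whether the outcome change differs between the IG and the CG".

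**The concern.** Low mood, anxiety and binge eating can worsen in bulimia nervosa without any intervention. A percentage from one arm, filtered by the participant's belief about cause, can err in both directions. It drops real deterioration that the participant blames on something else, and it counts ordinary fluctuation that the participant blames on the programme. Attribution is harder still because section 2.3.3 allows other treatments in both groups. It is also not blind: under section 2.3.1 each participant is told by email whether access starts now or in 12 weeks.

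At stake is how the trial's safety statement can be read. Section 3.1 says that there is no empirical evidence yet for the effectiveness of this particular programme, so this trial may supply the first safety figure. As planned, that figure would be reported as caused by the intervention without a comparison that could support the claim.

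**Working it through.** **1. What each planned quantity can show.**

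| Quantity | Arms | What it answers |
|---|---|---|
| NEQ percentage and impairment (2.5.3) | Intervention only | How many participants believe that the programme harmed them, and how much |
| Treatment × time interaction (2.5.1) | Both | Whether average change differs between arms |
| Proportion of individuals who deteriorate | Not stated | Whether more people get worse with the programme than without it |

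The second row does not replace the third, because an average benefit can coexist with a subgroup that deteriorates.

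**2. The plan's own figure.** The article gives no safety rate or safety precision, so none can be reproduced. Its N = 152 can be, and this fixes the arm size used below. Inputs from section 2.6: d = 0.50, ICC .40, power .80, alpha .05 (two-sided assumed). With total SD 1, the residual variance is 1 − 0.40 = 0.60. With times 0, 0.5 and 1, the sum of squares of time is 0.5. The per-patient slope SD is √(0.60/0.5) = 1.095, and n per arm = 2 × (1.960 + 0.842)² × 1.095² / 0.50² ≈ 75.4, rounded up to 76. The total is 152, which agrees.

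**3. Precision of a between-arm comparison.** The rates are assumed, equal in both arms, with 76 per arm (1:1 allocation, section 2.3.1) and no dropout. Half-width of the 95% interval for the risk difference = 1.96 × √(2p(1 − p)/76). For one arm alone it is 1.96 × √(p(1 − p)/76).

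| Assumed rate p | One arm alone | Risk difference |
|---|---|---|
| 5% | 4.9 points | 6.9 points |
| 10% | 6.7 points | 9.5 points |
| 20% | 9.0 points | 12.7 points |
| 30% | 10.3 points | 14.6 points |

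The one-arm interval is narrower, but it contains no comparison.

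**4. Power, if someone wished to test.** Two-proportion normal approximation, two-sided 5%, 76 per arm.

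| Control rate | 10-point excess | 20-point excess |
|---|---|---|
| 5% | 0.54 | 0.94 |
| 10% | 0.41 | 0.88 |
| 20% | 0.30 | 0.77 |
| 30% | 0.25 | 0.72 |

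**5. Illustration of why a worsening rate needs its control and a threshold.** Assume normal scores, ICC .40 and baseline SD 1. The SD of the change from baseline to week 12 is √(2 × 0.60) = 1.095.

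- Worse by at least 0.5 SD, no true change: 1 − Φ(0.5/1.095) = 32%.
- Worse by at least 0.5 SD, mean improvement of 0.5 SD: 1 − Φ(1.0/1.095) = 18%.
- Any worsening at all: 50% and 1 − Φ(0.5/1.095) = 32%. Without a threshold, noise dominates.

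At 32% and 18% the half-width of the risk difference is 1.96 × √((0.324 × 0.676 + 0.181 × 0.819)/76) = 13.6 points, about the size of the 14-point difference itself.

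**The case against.** The other side has four good arguments.

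- **The control arm is used.** A reader might infer that harm cannot be separated from the natural course at all. The article does not support that. The treatment × time models cover the same symptom measures, and an interaction in the wrong direction would be evidence of net worsening relative to control. What is absent is the comparison of individual deterioration.
- **NEQ data from controls may not exist.** A reader might take Table 2 to show that both arms complete the NEQ, especially as section 2.4.7 limits a different item to one arm ("participants in the IG will be asked how many times they used the intervention in the study assessments after six and 12 weeks"). But Table 2 also gives the intervention and the waiting time identical marks, so the lack of an arm restriction proves nothing. An instrument for effects of an intervention has a natural reason to be summarised only among those who have access.
- **The 32% and 18% are not planned results.** A reader might infer that the trial will report an 18% deterioration rate that looks like harm. It will not: the plan reports attributed NEQ effects and no deterioration rate. The calculation also assumes normal scores, whereas the primary outcomes are episode counts.
- **A fuller safety analysis may sit elsewhere.** Deterioration definitions are often left to an analysis plan, and the article points to an R script that is not shown.

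The first three arguments stand and limit the point. The fourth stands only in part. The missing deterioration table, taken alone, could be left to another document. But the article itself fixes the arm, the attribution filter and the causal wording of its safety indicators, and those are what is at issue.

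**Conclusion.** The point holds in a limited form. Both stated safety indicators are single-arm and depend on unblinded self-attribution. They do not support describing effects as caused by the intervention, and they miss worsening attributed to anything else. The article states a between-arm comparison of means but none of individual deterioration, although the outcomes needed are scheduled at 0, 6 and 12 weeks without restriction to one arm.

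The efficacy analysis is not affected. The change is worth making because it is cheap and avoids an unsupported causal safety claim, but its yield is modest. With 76 per arm the half-width of the risk difference is about 7 to 15 points for rates of 5% to 30%, and power for a 10-point excess is 0.25 to 0.54. These figures rest on assumed equal rates and no dropout. Section 3.1 itself names high dropout as a possible challenge, so the real intervals would be wider.

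**What to change.** 1. In section 2.5.3, describe the two NEQ figures as effects that participants in the intervention group attribute to the intervention, and keep them as descriptive.
2. Add a between-arm safety indicator in all randomised participants: the proportion in each arm that deteriorates from baseline to week 6 and to week 12 on binge count, compensatory-behaviour count, EDE-Q total and PHQ-9. Fix one threshold before group labels are revealed, for example at least 0.5 baseline SD worse, or reliable change, and do not count any worsening at all. Report each risk difference with its 95% confidence interval as estimation, without a test.
3. State which arms complete the NEQ. Only if controls do, also report negative effects by arm regardless of attribution.

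The cost is a short addition to the analysis script and one table from outcomes already scheduled, with no extra visits and no change to the primary analysis. The downsides are wide intervals, eight related estimates (four outcomes at two time points) that must be read together, and a safety statement that may prove less favourable.
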